**14. BIOLOGICAL CORRELATES**

Several recent studies demonstrated predictive value of circulating VEGF after treatment with radiation. High levels of VEGF prior to radiation and failure of VEGF to decrease after radiation have been correlated with poor outcomes after radiation. To determine if blood or urine VEGF levels predict for outcome in patients treated on this protocol, peripheral blood and urine will be collected prior to and after radiation and Sutent. For the pre-treatment and post-treatment blood collections, 19 ml of blood will be collected from each patient: two 5 ml red top tubes; one for serum extraction and one to go with the two 4.5 ml purple EDTA tubes for DNA analysis. Serum extraction will require a centrifuge, pipette and -70° C freezer for storage.

Serum and urine VEGF before and after radiation + Sutent will be measured by a commercially available ELISA kit and correlated with outcome (Oncogene Research). Additionally, the Mount Sinai Radiation Biology division has significant experience with screening for genetic polymophisms using denaturing high performance liquid chromatography and Surveyor nuclease assays (39). Therefore, we propose using this technology to analyze specific VEGFR polymorphisms from peripheral blood samples of treated patients to determine there is any correlation with outcome for any specific or class of genetic variants.

Serum/blood will be analyzed for the translational research component of this protocol and will be stored for future studies. If at any time the patient withdraws consent to store and use specimens, the material will be destroyed.

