**12. TOXICITY**

- Radiation side effects are limited to the area involved in the treatment field(s). Acute and late toxicity related to radiation therapy include fatigue, nausea and vomiting, myelosuppression, skin erythema, subcutaneous fibrosis, esophagitis, pericarditis, diarrhea, cystitis, proctitis, myelitis, acute radiation pneumonitis, late pulmonary fibrosis, esophageal stricture, liver dysfunction, kidney damage, small bowel obstruction.
- Sutent toxicities are discussed in detail in Section 9.7
- Grade 3-5 non-hematological toxicities (excluding nausea, vomiting, and alopecia) and Grade 4-5 hematological toxicities will be referred to as dose limiting toxicities (DLT).
  - Esophagitis and mucositis are very common side effects with radiation therapy and grade 3 side effects can be seen after palliative courses of radiotherapy. Therefore, grade 3 mucositis or esophagitis lasting ≤ 7 days will not be considered a DLT. If the grade 3 mucositis or esophagitis lasts > 7 days, it will then be considered a DLT.
- All life-threatening Grade 4 and all fatal toxicities (Grade 5) must be reported immediately and evaluated.
- Acute toxicity: Acute side effects are considered as occurring ≤ 30 days from the start of radiation therapy. They will be documented using the NCI Common Terminology Criteria for Adverse Events (CTCAE) version 3.0 (A copy can be downloaded from [http://ctep.info.nih.gov](http://ctep.info.nih.gov/)).
- Late toxicity: Late side effects are considered occurring > 30 days from the start of radiation therapy. They will be evaluated and graded according to the RTOG Late Morbidity Scoring Scale (See Appendix).

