**2. Summary of Method – Urine Collection**

Mid-stream urine is obtained by standard urine collection techniques into a sterile container.

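### Before-after VEGF is fixed to serum and spot urine with no plasma aliquot, urine creatinine or set sampling day, so a change may partly reflect platelet loss or urine dilution

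*Protocol*

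**What the plan says.** Section 14 sets out to learn whether blood or urine VEGF predicts outcome. The background it cites covers both a high level before radiation and the change afterwards; on the change it says that "failure of VEGF to decrease after radiation have been correlated with poor outcomes after radiation". A fall is therefore the favourable direction.

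The measurement is stated as: "Serum and urine VEGF before and after radiation + Sutent will be measured by a commercially available ELISA kit and correlated with outcome". Each blood collection consists of "two 5 ml red top tubes; one for serum extraction and one to go with the two 4.5 ml purple EDTA tubes for DNA analysis". Processing is described by equipment only: "Serum extraction will require a centrifuge, pipette and -70° C freezer for storage". Timing is given as "peripheral blood and urine will be collected prior to and after radiation and Sutent", with no day for the second sample.

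The blood and urine collection SOP names no tube type and no plasma step. For urine it says: "Mid-stream urine is obtained by standard urine collection techniques into a sterile container". No urine creatinine appears in the SOP, in Section 14 or in the test lists of Section 7; the biochemistry there is a metabolic profile of the blood-chemistry kind.

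Two other places bear on the point. Section 12 says: "Acute and late toxicity related to radiation therapy include fatigue, nausea and vomiting, myelosuppression", and the same section counts grade 4-5 hematological toxicity as dose limiting. A CBC with platelets is scheduled before therapy, weekly during treatment, and at follow-up visits every 2 weeks for the first 2 months (Sections 7.1, 7.2 and 7.4).

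**The concern.** Serum is what remains after blood has clotted. If platelets release VEGF as they clot, serum VEGF is a mixture of VEGF that was circulating and VEGF released in the tube, and the second part moves with the platelet count. Treatment that lowers platelets would then lower serum VEGF with no change in the tumour, in the direction Section 14 treats as good. The marker would be tied in part to marrow toxicity. Marrow toxicity may depend on dose level and on recent chemotherapy, and either may be related to outcome in its own right.

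The undefined second sampling day adds to this. The synopsis allows chemotherapy from day 43, so samples from different patients could fall before or after chemotherapy has begun.

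For urine, the concentration in a single mid-stream sample depends on hydration. Two such samples carry two independent dilution errors, which weaken any real association in a cohort of 52 (synopsis) or 50 to 65 (Section 16).

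The blood part is a bench decision. Plasma that was never separated cannot be recovered by a later analysis plan. Drawing the EDTA tubes at both visits for DNA alone also gains little, because a polymorphism does not change between visits.

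**Working it through.** **No figure in the plan to reproduce.** Section 14 gives no sample size, power or cut-off for VEGF. The tube volumes do add up: 2 × 5 + 2 × 4.5 = 19 ml, the stated total. The EDTA share is 2 × 4.5 = 9 ml per collection, so plasma could come from blood already planned.

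**Inputs from the protocol:** the matrices, the tube assignment, the favourable direction, and myelosuppression as a listed toxicity.

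**Inputs that are assumptions:** the platelet-derived share of serum VEGF (f), the platelet fall (d), the urine dilution SD per sample on the log scale (s), and the SD of the true log change in urine VEGF (0.7).

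**Step 1, serum.** Hold circulating VEGF constant. Apparent change in serum VEGF = −f × d. For a halved platelet count, d = 0.5:

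| Platelet share f | Apparent serum change |
|---|---|
| 0 | 0% |
| 0.2 | −10% |
| 0.5 | −25% |
| 0.8 | −40% |
| 1.0 | −50% |

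Over platelet falls of 10% to 70% and shares of 0.2 to 0.8, the range is −2% (0.2 × 0.1) to −56% (0.8 × 0.7).

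**Step 2, how closely serum change follows platelet change.** Simulation with serum ratio = f × platelet ratio + (1 − f) × free VEGF ratio, both ratios log-normal. The log platelet ratio has mean −0.3 and SD 0.3. The log free VEGF ratio has mean 0 and SD 0.2 or 0.5.

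| f | Correlation, SD 0.2 | Correlation, SD 0.5 |
|---|---|---|
| 0 | 0.00 | 0.00 |
| 0.2 | 0.28 | 0.12 |
| 0.5 | 0.74 | 0.41 |
| 0.8 | 0.97 | 0.84 |

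The link runs from none to nearly complete, depending on a share the documents do not give.

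**Step 3, urine in one patient.** With excretion unchanged, apparent change = 1/r − 1, where r is the post/pre dilution ratio. For r = 0.5, 1.5, 2 and 3 this gives +100%, −33%, −50% and −67%.

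**Step 4, urine across the cohort.** If the dilution errors of the two samples are independent of each other and of outcome, the correlation of measured change with outcome is multiplied by 0.7 / √(0.7² + 2s²):

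- s = 0.2: 0.7 / √0.57 = 0.93
- s = 0.4: 0.7 / √0.81 = 0.78
- s = 0.6: 0.7 / √1.21 = 0.64
- s = 0.8: 0.7 / √1.77 = 0.53

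**The case against.** The strongest reply is that the mechanism and every magnitude come from outside the protocol. Nothing in the document says platelets release VEGF on clotting. No platelet fall is quantified: myelosuppression appears in a general list of radiation effects, the Sutent adverse-effect text in Section 9.7 names no hematological toxicity, and Section 8 limits the marrow irradiated. This stands. It is why the mechanism is stated as an assumption and the range starts at a negligible effect.

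Platelet counts are already scheduled, so serum can be adjusted in analysis with little or no new data. This also stands, with one gap: with no sampling day fixed, a matching count is likely but not assured.

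Urine normalisation and covariates can be set in a laboratory manual or in the analysis plan, which is not shown. For urine this largely holds. The protocol is silent rather than committed to raw concentrations, and stored urine could be assayed for creatinine later. It does not hold for plasma, because the protocol itself assigns the EDTA tubes to DNA.

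Two limits on reach are fair. The platelet fall caused by treatment cannot distort the pre-treatment VEGF level, the other predictor Section 14 names. Confounding by dose level is also weaker in the phase II patients, who are meant to share one level.

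A reader might go further and infer that myelosuppressed patients will be labelled VEGF responders. The protocol does not support that: it defines no responder class, no cut-off and no decision based on VEGF, and plans only a correlation with outcome.

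**Conclusion.** The point holds as a minor one. The protocol fixes serum and spot urine for before-after VEGF, plans no plasma, and lists neither a urine creatinine nor a post-treatment sampling day. A before-after fall may therefore partly reflect platelet loss or dilution.

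The size depends on assumptions: for a halved platelet count, an apparent serum fall of about 10% at a platelet share of 0.2 and 40% to 50% at shares of 0.8 to 1.0; for urine, attenuation of about 0.93 to 0.53. It would be too strong to say that the change will track platelets and dilution, since at a platelet share near zero or a small dilution SD the effect is negligible.

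VEGF is not among the objectives in Section 1 and is not mentioned in Section 16. The MTD, PFS and OS analyses are untouched.

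**What to change.** In Section 14 and the collection SOP:

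1. Separate plasma from the EDTA tubes already drawn, take DNA from the remaining cells, and measure VEGF in plasma alongside serum.
2. Analyse serum VEGF with the platelet count from the scheduled CBC nearest the sample as a covariate.
3. Fix the post-treatment sampling day so that it coincides with a scheduled CBC.
4. Measure creatinine in the same urine aliquot and analyse urine VEGF per mg creatinine.

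The cost is one extra spin and one inexpensive assay, with no added blood volume, visit or patient. The downside is that plasma VEGF lies nearer the assay limit than serum VEGF, which is why serum should be kept.

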**15. ADVERSE EVENTS**

- - A **serious adverse event** (experience) or reaction is any untoward medical occurrence that at any dose: results in death, is life-threatening, requires inpatient hospitalization or prolongation of existing hospitalization, results in persistent or significant disability / incapacity, or is a congenital anomaly / birth defect.
  - The definition of serious adverse event (experience) also includes *important medical event*. Medical and scientific judgment should be exercised in deciding whether expedited reporting is appropriate in other situations, such as important medical events that may not be immediately life-threatening or result in death or hospitalization but may jeopardize the patient or may require intervention to prevent one of the other outcomes listed in the definition above. These should also usually be considered serious.
- Mount Sinai School of Medicine Reporting Guidelines
  - If the reaction requires reporting, the [name] or fellow reports adverse reaction to the patient data management office [contact]) by the end of the business day when he/she becomes aware of the event. Events occurring after business hours will be reported to the patient data management office by 12 pm (noon) the next business day.
  - The following information is required when calling in the event:
    - Caller’s Name and Telephone Number, Patient Initials, Patient Medical Record Number, IRB Protocol Number, PI of Study, Attending Physician, Date of Event, Description of Event (including grade of the event and if the event required hospitalization)
  - E-mail is sent to the research nurse, attending physician and PI of the study informing them that adverse reaction notification has been received.
  - Required protocol documents must be sent to the data management office along with Mount Sinai’s IRB Adverse Event Form within **5 working days of event occurrence**. Once the forms are completed forward the original to the study PI. The PI will then review, sign and place folder in the QA Coordinator’s box. A weekly report of delinquent or pending documents will be forwarded to the principal investigator. All delinquent reporting (greater than 10 days from event occurrence) must include documentation of reason for delinquency and may require implementation of an action plan.
  - Once the appropriate AE documents have been received, the principal investigator forwards these to the IRB (Mount Sinai only), affiliate institutions if applicable. A copy will be forwarded to the appropriate Research Nurse.
- Data Safety and Monitoring
  - Data Safety and Monitoring will occur at the biweekly Mount Sinai School of Medicine, Department of Radiation Oncology phase I/II quality assurance meetings, which are lead by the department chairman ([name].) and include a medical oncologist ([name].) and patient advocate. At each meeting, all active studies will be reviewed for safety and progress toward completion. Toxicities and adverse events will be reviewed at each meeting and a Data Safety and Monitoring form will be completed for each protocol and signed by either the principal investigator, the chairman of the department or by his designate if the chairman is not available.

**15.1 Serious Adverse Event (SAE) Reporting to Pfizer**

Within 24 hours of first awareness of the event (immediately if the event is fatal or
life-threatening), Principal Investigator will report to the Pfizer by facsimile any Serious Adverse Event ("SAE," as defined below) that occurs during the SAE reporting period (as defined below) in a Study subject assigned to receive the Pfizer Product.  Principal Investigator will report such SAEs using an FDA MEDWATCH form and the Serious Adverse Event Fax Cover Sheet provided by Pfizer.  SAEs should be reported as soon as they are determined to meet the definition, even if complete information is not yet available. 

*SAE Definition:*  An SAE is any adverse event, without regard to causality, that is life-threatening or that results in any of the following outcomes: death; in-patient hospitalization or prolongation of existing hospitalization; persistent or significant disability or incapacity; or a congenital anomaly or birth defect.  Any other medical event that, in the medical judgment of the Principal Investigator, may
jeopardize the subject or may require medical or surgical intervention to prevent one of the outcomes listed above is also considered an SAE. A planned medical or surgical procedure is not, in itself, an SAE.  Also specifically excluded from this definition of SAE is any event judged by the Principal Investigator to represent progression of the malignancy under study, unless it results in death within the SAE Reporting Period.

*SAE Reporting Period:* The SAEs that are subject to this reporting provision are those that occur from after the first dose of the Pfizer Product through 28 days after discontinuation of the Pfizer Product. 

*Follow-Up Information:*  Institution will assist Pfizer in investigating any SAE and will provide any follow-up information reasonably requested by Pfizer.

*Regulatory Reporting:*  Reporting an SAE to Pfizer does not relieve
Institution of responsibility for reporting it to regulatory
authorities, as required.

**16. STATISTICAL CONSIDERATIONS**

- Phase I: The primary objectives are to determine the maximum tolerated dose (MTD) and dose limiting toxicity (DLT) of extracranial stereotactic radiation therapy in combination with Sutent when given to all sites of involved disease in patients with metastatic cancer.
- For dose escalation purposes, the major endpoint will be dose-limiting toxicity occurring within 30 days after the start of radiation therapy.
- Dose limiting toxicity is defined as follows: Grade 3-5 non-hematological toxicities (excluding nausea, vomiting, and alopecia) and Grade 4-5 hematological toxicities.
  - Esophagitis and mucositis are very common side effects with radiation therapy and grade 3 side effects can be seen after palliative courses of radiotherapy. Therefore, grade 3 mucositis or esophagitis lasting ≤ 7 days will not be considered a DLT. If the grade 3 mucositis or esophagitis lasts > 7 days, it will then be considered a DLT.
- The MTD for a specific area will be exceeded if 2 or more patients out of 6 (or a third or more) with disease at that site experience DLT at that dose. The dose immediately below will be recommended for further study.
- Phase II: *(Includes 3 to 6 patients from Phase I MTD):* The median progression free survival with optimal chemotherapy alone for the 4 most common tumor types (lung, breast, prostate and colorectal) ranges from 2.2 to 10.6 months, depending on primary tumor site and degree of pretreatment. Therefore, we will assume a median time to progression of 6.4 months (standard deviation 3.2 months) with chemotherapy alone. With 38 patients, this study has 87% power (α=0.05) to detect a 25% increase in time to progression. Also the 2 year freedom from progression is <5% with chemotherapy therapy and this study has 70% power (α=0.05) to demonstrate a 10% absolute increase in 2 year progression-free survival.
  - All patients included in the study will be assessed for response to treatment, even if there are major protocol treatment deviations or if they are ineligible (intent-to-treat population). Criteria described in Section 10 will be used to assign each patient to one of the following response categories: 1) complete response, 2) partial response, 3) stable disease, 4) progressive disease, 5) early death from malignant disease, 6) early death from toxicity, 7) early death because of other cause, or 8) unknown (not assessable, insufficient data).
  - All patients who have met the eligibility criteria will be included in the main analysis of the response rate. Patients in response categories 4 – 8 will be considered as failing to respond to treatment (disease progression).
  - All individual lesions will also be recorded as CR, PR, SD, or PD.
  - Overall survival is the time from the date of first study treatment until death from any cause.

Overall survival and progression-free survival (PFS) will be calculated using the Kaplan-Meier (1958) estimator.(40) Median survival times and their associated 90% confidence intervals will be derived using the method described in Brookmeyer and Crowley (1982).(41)

The percentage of patients with complete responses and the percentage with complete or partial responses will be calculated and confidence intervals derived. The pattern of failures (local or distant) will be summarized. Adverse effects will also be tabulated by type and level of severity. Potential prognostic variables, such as number of lesion sites at baseline, will be examined by fitting Cox (1972) regression models for progression-free and overall survival times.(42) Given the sample size, only univariate analysis will be performed.

- Accrual Rate and Study Duration
  - The estimated accrual will depend on toxicity encountered, but we anticipate enrolling 50-65 patients.
  - We anticipate enrolling 1-3 patients per month.

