**Treatment Plan**:

- Sutent be administered PO QD from days 1 to 28 (see Figure 1)

Figure 1. Treatment Schema

Determine eligibility

**↓**

| **REGISTER** | **Treatment** | Days  1-7 | 8-12 | 13-14 | 15-19 | 20-28 | 29-42 |
| --- | --- | --- | --- | --- | --- | --- | --- |
| XRT |  | X |  | X |  |  |
| Sutent | X | X | X | X | X |  |

**↓**

Additional chemotherapy (as determined by Medical Oncology)

**↓**

Maintenance Sutent (until death or progression) and appropriate follow-up

- Radiation therapy will start on day 8 and will be given to each site for ten fractions
- Fractions must be separated by at least 16 hours
- The MTD of radiation in combination with Sutent will be determined
- Doses of radiation and Sutent will increase as shown in Table 1 in order to determine the MTD of radiation in Gy and Sutent in mg
- The RPTD will be one dose level lower than the MTD. If the MTD is not reached at dose level 5, no further escalation will occur and this will be the RPTD. The RPTD will then be used for future phase II trials.
- Starting day 43, chemotherapy may be given, as determined by the treating medical oncologist.
- Two weeks after completion of any chemotherapy, maintenance Sutent in 6 week cycles (consisting of Sutent 50 mg PO QD weeks 1-4 followed by no treatment weeks 5-6) until progression or death
- If no chemotherapy is planned, maintenance Sutent (as described above) will start on day 43.

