**Statistical analysis:**

*Phase I: Feasibility and toxicity.* Patients will receive concurrent treatment with extracranial radiosurgery and Sutent. Both the radiation dose and Sutent dose will be escalated as the trial progresses from Levels 1 through 5 as shown in Table 1. The starting radiation dose is 40 Gy in 10 fractions and the starting Sutent dose is 25 mg PO QD. The dose escalation strategy is as follows: The trial will start with dose level 1. At each level, 3 patients will be treated and their toxicities will be assessed. If no patients experience dose limiting toxicity, the trial will proceed to the next dose level. If 1 patient develops unexpected acute toxicity at any dose level, an additional 3 patients will be treated at that dose level. If ≥2 patients experience unexpected toxicity, the previous dose level will be declared the maximal tolerated dose for Phase II evaluation

*Phase II (Includes 3 to 6 patients from Phase I MTD):* The median progression free survival with optimal chemotherapy alone for the 4 most common tumor types (lung, breast, prostate and colorectal) ranges from 2.2 to 10.6 months, depending on primary tumor site and degree of pretreatment. Therefore, we will assume a median time to progression of 6.4 months (standard deviation 3.2 months) with chemotherapy alone. Using the data from this trial, response rates will be estimated and Kaplan-Meier curves generated for progression-free and overall survival (1). With 38 patients for the phase II portion, this study has 87% power (α=0.05) to detect a 25% increase in time to progression. Also the 2 year freedom from progression is <5% with chemotherapy therapy and this study has 70% power (α=0.05) to demonstrate a 10% absolute increase in 2 year progression-free survival.

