11. Radiation is to be delivered to each site over 10 fractions separated by at least 16 hours. Up to 5 sites may be treated. **(Added 7/27/06)** For patients with 3 to 5 sites of disease, it may be difficult to treat all sites of disease during one day. For these patients, an acceptable variant is to treat all 2 to 3 sites during days 8 to 19 and to treat the remaining sites on days 20 to 33. For these patients only, concurrent Sutent will continue until day 42.
12. Radiation Doses (Phase I): A phase I escalation of doses will be performed in order to determine in MTD in Gy

Doses of radiation will increase as follows in order to determine the MTD of radiation in combination with Sutent:

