**Table 1. Phase I Dose Levels**

| **Dose Level** | **Radiation Dose** | **Sutent Dose** |
| --- | --- | --- |
| 1 | 40 Gy in 10 fractions | 25 mg PO QD |
| 2 | 40 Gy in 10 fractions | 37.5 mg PO QD |
| 3 | 50 Gy in 10 fractions | 37.5 mg PO QD |
| 4 | 50 Gy in 10 fractions | 50 mg PO QD |
| 5 | 60 Gy in 10 fractions | 50 mg PO QD |

.

Phase I dose escalation will proceed according to a “3+3” design. After 3 patients have been treated on each dose level, they will be followed for at least 30 days. If 0 of 3 patients have DLTs, the dose will be escalated to the next dose level. If ≥2 of 3 patients have DLTs, dose escalation will be terminated and the next lowest dose level will be declared the maximal tolerated dose for Phase II evaluation. If 1 of 3 patients has a DLT, then three more patients will be treated at the same dose level and if the incidence of DLT among six patients is < 2 of 6, the dose will be escalated to the next level for that site.

- Grades 3-5 non-hematological toxicities (excluding nausea, vomiting, and alopecia) and Grade 4-5 hematological toxicities will be referred to as dose limiting toxicities (DLT).
  - Esophagitis and mucositis are very common side effects with radiation therapy and grade 3 side effects can be seen after palliative courses of radiotherapy. Therefore, grade 3 mucositis or esophagitis lasting ≤ 7 days will **not** be considered a DLT. If the grade 3 mucositis or esophagitis lasts > 7 days, it will then be considered a DLT.
- The recommended phase II dose will be 1 dose level below the defined MTD or at the maximum tested dose if the MTD has not been reached.

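### Section 16 counts DLTs for escalation only from radiation start (days 8 to 38); as written it omits the Sutent-only lead-in and the end of the multi-site variant

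*Protocol*

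**What the plan says.** - **Endpoint.** Section 16 (Phase I) states that, for escalation, "the major endpoint will be dose-limiting toxicity occurring within 30 days after the start of radiation therapy".
- **Standard schedule.** Sutent is taken on days 1 to 28. The synopsis (Treatment Plan) adds: "Radiation therapy will start on day 8 and will be given to each site for ten fractions". The schema places the fractions on days 8–12 and 15–19.
- **Multi-site variant.** Section 8.1, item 11, lets patients with 3 to 5 sites have some sites treated on days 8 to 19, and then "treat the remaining sites on days 20 to 33". It adds: "For these patients only, concurrent Sutent will continue until day 42".
- **Dose steps.** In Table 1, level 2 is "40 Gy in 10 fractions | 37.5 mg PO QD", the same radiation as level 1 with Sutent raised from 25 mg. Level 4 is "50 Gy in 10 fractions | 50 mg PO QD", the same radiation as level 3 with Sutent raised from 37.5 mg.
- **Escalation rules.** Section 10 defines a DLT by grade with no time limit, and says: "After 3 patients have been treated on each dose level, they will be followed for at least 30 days". It does not say from which day the 30 days run.
- **Synopsis (Statistical analysis).** "If no patients experience dose limiting toxicity, the trial will proceed to the next dose level". This sentence and the stopping sentence carry no time limit. Only the sentence that adds three patients speaks of acute toxicity.
- **Section 12** divides acute from late toxicity at the same point, 30 days from the start of radiation.

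**The concern.** Section 1 sets out to find the MTD of the combination, in Gy and in mg of Sutent. Drug exposure at the assigned level begins a week before radiation, yet the only passage that dates the toxicity that counts starts its clock at radiation. When a step raises Sutent alone, any new toxicity comes from the drug or its interaction with radiation, and the first week on the new drug dose lies outside the window.

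One case is starker. Section 6 allows a patient to be taken off treatment for an adverse event at any time. If that happens in days 1 to 7, radiation never starts, and read literally the Section 16 window never opens. A lead-in toxicity severe enough to stop treatment could not then count.

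On the variant the clock also stops while the patient is still on concurrent Sutent. In a 3+3 design a single event decides the outcome: leaving one out turns 1 of 3 (expand) into 0 of 3 (escalate), or 2 of 3 (stop) into 1 of 3 (expand).

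**Working it through.** The 30 days are a definition, so there is no stated figure to reproduce. The check is a count of days.

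**Inputs.** Radiation starts on day 8 (synopsis, Treatment Plan). Standard schedule: last fraction day 19, last Sutent dose day 28. Variant: last fraction day 33, Sutent until day 42 (Section 8.1, item 11).

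**Window.** Day 8 + 30 = day 38.

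| | Standard | Variant |
|---|---|---|
| Sutent days before the window | 7 (days 1–7) | 7 (days 1–7) |
| Window close minus last fraction | 38 − 19 = 19 days | 38 − 33 = 5 days |
| Window close minus last concurrent dose | 38 − 28 = 10 days | 38 − 42 = −4 days |
| Concurrent Sutent days outside the window | 7 of 28 | 7 + 4 = 11 of 42 |

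**Sensitivity to the counting rule.** If day 8 counts as the first of the 30 days, the window ends on day 37 and the late gap on the variant is 5 days. If Sutent until day 42 means a last dose on day 41, the gap to day 38 is 3 days. So the late gap is 3 to 5 days; the 7-day lead-in gap does not change.

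**Steps that raise only Sutent.** Level 1 to 2: 37.5 / 25 = 1.50, or +50%. Level 3 to 4: 50 / 37.5 = 1.33, or +33%. These are 2 of 4 steps.

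**Where Section 10's 30 days could end.**

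| Counted from | Standard | Variant |
|---|---|---|
| Start of radiation | day 38 | day 38 |
| Last fraction | 19 + 30 = day 49 | 33 + 30 = day 63 |
| Last concurrent Sutent dose | 28 + 30 = day 58 | 42 + 30 = day 72 |

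**Matching the variant to the standard schedule.** For 19 days after the last fraction: 33 + 19 = day 52. For 10 days after the last concurrent dose: 42 + 10 = day 52. Both give the same day.

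**The case against.** The best defence is that Section 10, not Section 16, is the operating rule. It speaks of patients who have been treated and are then followed for 30 days, which most naturally means follow-up after treatment, to day 49 or later. Its DLT definition excludes neither days 1–7 nor days 39–42. Section 16 calls its endpoint the major one, not the only one. An investigator following Section 10 could count every event at issue. This stands, and it means that a loss of DLTs is possible but not shown. It does not cure the text: how long a patient is watched and which events decide escalation are separate matters, and only Section 16 dates the second.

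It can also be said that the radiation anchor suits a combination MTD, because days 1–7 are Sutent alone at doses no higher than the 50 mg/day single-agent MTD cited in Section 2c. A lead-in toxicity that persists would still be seen after day 8. Both points limit the harm. They do not help with the patient who never reaches radiation, and Section 2c itself says that no clinical study of Sutent with radiation had been reported.

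Three stronger readings are tempting and not supported:

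- *About a quarter of DLTs are missed.* The shares 7/28 (25%) and 11/42 (26%) are shares of calendar days. The protocol gives no timing of DLT risk.
- *The MTD will be set too high.* Dropping events under Section 16 can only favour escalation. But Section 10's undated rule could also admit toxicity from 50 mg maintenance Sutent, which may start on day 43 and exceeds the assigned dose at levels 1–3. That would work the other way. The net direction depends on which section is followed.
- *The events go unseen.* Section 7.2 asks for weekly adverse-effect assessment during treatment, and Section 15.1 collects SAEs from the first Sutent dose.

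**Conclusion.** The point holds and should be fixed. As written, Section 16 omits the 7-day Sutent lead-in for every phase I patient. On the optional variant it closes 5 days after the last fraction and about 4 days (3 to 5, by counting rule) before the last concurrent dose. The close on the standard schedule is adequate, at 19 and 10 days. Sections 10 and 16 can be read differently on which DLTs count, so the same patient could lead to different escalation decisions.

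The effect on MTD selection cannot be derived: neither the timing of DLTs nor the uptake of the variant is given. The practical harm is limited by the dose ceiling and by the recording of events. The conclusion rests on the schema's day numbering and on reading Section 16 literally.

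**What to change.** In Sections 10 and 16, define one DLT window that:

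- opens with the first Sutent dose (day 1) and counts a DLT even if radiation is never started;
- closes no earlier than day 38 on the standard schedule and day 52 on the variant.

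Name the anchor of Section 10's minimum 30-day follow-up without shortening it. Do not escalate, or select the phase II dose, until the window has closed for every patient at the level. Because Section 12 moves toxicity after day 38 to the late-morbidity scale, add a line saying which scale grades a DLT on days 39 to 52 of the variant.

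Treat toxicity that arises after maintenance Sutent or chemotherapy begins by attribution, not by date, and exclude it only if judged due to that later treatment rather than to the concurrent course. A cut at day 43 would be wrong: a variant patient is then only 43 − 33 = 10 days past the last fraction and 1 day past the last concurrent dose. Section 11.1 already excludes toxicity resulting from non-protocol therapy, but maintenance Sutent is protocol therapy and needs its own sentence.

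**Cost.** Amendment wording, plus some judgement on attribution from day 43 to day 52 of the variant. If the present wait ends on day 38, the standard schedule has no added wait, and a cohort review in which a variant patient is the last one followed waits up to 52 − 38 = 14 days more. As a ceiling, if that happened at every review: 5 × 14 = 70 days with three patients at each of the five levels, or 10 × 14 = 140 days if every level expanded to six. Against the 1,704 days from 1/1/2007 to 9/1/2011, that is 4.1% or 8.2%. If Section 10's follow-up already runs from the last fraction or the last concurrent dose, nothing is added.
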